### Data analysis

#### Feasibility

We collect the following feasibility measures and will report them descriptively [28]: number of patients screened, proportion eligible, number of patients recruited, time required to recruit, number of patients unable to provide consent, number of patient refusals, number of dropouts, and retention at each follow-up time point. We will use frequencies, proportions, rates, means/medians, and standard deviations and other measures of variability, as appropriate, to report on these feasibility measures. Also, we keep a record of lessons learned during the implementation of this study. To compare the median ED LOS between participants in both study arms, we will use the Wilcoxon-Mann-Whitney test and bootstrapping to generate a 95% confidence interval for the median difference in ED LOS. We will also examine the length of time required to complete the pharmacy and PT consultation in the intervention arm to determine if the intervention is feasible within the timeframe of an ED visit.

#### Fidelity

We will use descriptive statistics to assess key parameters of fidelity: receipt of the pharmacy and PT consultations, MRAP provision to patients and receipt of the MRAP by PCPs, fall calendar completion, and uptake of recommendations by patients and PCPs at 6-month follow-up. Implementation activities will be measured against recommendations and categorized into three level of adherence: adherent, partially adherent, and non-adherent.

#### Initial efficacy

We will complete the analyses on an intention-to-treat basis; participant outcomes will be analyzed according to their allocated arm, irrespective of the intervention received. Therefore, patients who are admitted or discharged to a skilled nursing facility after randomization will be included in the analysis.

We will compare the proportion and median/mean number of recurrent falls, ED visits, and hospital admissions over 6 months occurring in each arm using Fisher’s exact test (proportions) and Wilcoxon’s and Student’s *t* test (occurrence). If sample size permits, we will conduct a survival analysis for a time-to-event analysis. Survival time will be defined as the time from randomization to the time of the first recurrent fall. Dates and times for this outcome will be obtained from the fall calendar and EHR review. For this analysis, we will first use the Kaplan-Meier method to estimate time to the recurrent fall. Next, we will use the log-rank test to test differences between survival curves for the intervention vs. usual care arm. Finally, hazard ratios and 95% confidence intervals will be calculated using the Cox proportional hazards model; additional analyses will adjust for baseline differences in physical function. We may also use multivariate frailty models, which are an extension of traditional survival analyses that allow for multiple failures (in this case falls) and include random effects that take into account underlying individual predisposition to falling.

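### The firm efficacy analyses of falls, ED visits and admissions ignore follow-up time and give no rate ratio or dispersion to size the definitive trial

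*Protocol article*

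**What the plan says.** All the efficacy analyses stand in the protocol article under Data analysis, Initial efficacy.

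- **Firm analyses.** The plan is to "compare the proportion and median/mean number of recurrent falls, ED visits, and hospital admissions" between the two arms at the end of follow-up. Proportions and counts each have their own tests, "using Fisher’s exact test (proportions) and Wilcoxon’s and Student’s" (the last being the t test). The section promises intention-to-treat but does not mention person-time, rates or an offset.
- **Conditional analysis.** "If sample size permits, we will conduct a survival analysis for a time-to-event analysis". No threshold is given. It covers one outcome: "Survival time will be defined as the time from randomization to the time of the first recurrent fall".
- **Optional analysis.** "We may also use multivariate frailty models", for repeated falls only.
- **Adjustment.** In the Cox model, "additional analyses will adjust for baseline differences in physical function".

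Elsewhere in the article:

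- Purpose and methods says the pilot should supply initial efficacy estimates to help size the definitive trial.
- Feasibility lists "number of dropouts, and retention at each follow-up time point" among its measures, so incomplete follow-up is expected. No dropout rate is assumed.
- Follow-up procedures has masked staff review the electronic record to confirm and add to the fall calendars.
- Recruitment and enrollment stratifies randomisation by site.
- The Discussion says the study is not powered for a reduction in falls.

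**The concern.** A raw 6-month count means the same thing for two participants only if both were observed for 6 months. Some will not be. The trial does not exclude people with dementia, heavy chronic disease or poor prognosis, and calendars are collected only at the 180-day home visit. Participants know their arm, so retention could differ between arms.

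With the named tests, a partly followed participant can be handled in two ways. Dropping the participant loses information and departs from analysing everyone as randomised. Keeping the partial count treats unobserved time as free of events. ED visits and admissions have no time-based method at all, even a conditional one.

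The main use of these results is planning. A definitive trial with falls as the outcome needs an event rate, a rate ratio and a dispersion, and none of the firm analyses delivers these when follow-up varies. Tying adjustment to observed baseline differences adds a smaller problem: chance imbalance then decides the model.

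**Working it through.** The article gives no event rate, dispersion, dropout rate or power for these outcomes, so there is no figure of its own to reproduce. From the document: 60 per arm, 1:1 allocation, 6 months. Assumed: a 6-month mean of 0.5 to 1.0 falls, gamma-Poisson counts with dispersion k between 0 and 2, and dropouts leaving at a uniformly distributed time.

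**1. Partial counts analysed as they stand.** With dropout proportion d and a constant rate, mean exposure is 1 − d/2 of the full period.

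- 10% vs 30%: 0.85 / 0.95 = 0.89.
- 10% vs 40%: 0.80 / 0.95 = 0.84.

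These are apparent effects when there is none. Simulation at 60 per arm agrees (0.89 to 0.90, and 0.84 to 0.85), while the person-time ratio stays at 0.99 to 1.00. Rejection rates under no effect, at nominal 0.05, with mean 1.0 and k of 1 to 2:

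| Dropout | t | Wilcoxon | Fisher |
|---|---|---|---|
| 20% vs 20% | 0.047–0.055 | 0.046–0.055 | 0.032–0.035 |
| 10% vs 30% | 0.056–0.075 | 0.064–0.080 | 0.042–0.056 |
| 10% vs 40% | 0.077–0.088 | 0.090–0.098 | 0.057–0.073 |

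The negative binomial model with offset rejected 0.056 of the time at 10% vs 30% (k = 1).

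**2. Bias against noise.** With k = 1.5, mean 1.0 in both arms and full follow-up, the standard error of the log rate ratio is about √[(1/1 + 1/1 + 2 × 1.5)/60] = √(5/60) = 0.29. The bias is ln 0.89 = −0.12 or ln 0.84 = −0.17, about 0.4 to 0.6 of a standard error.

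**3. Dropping partly followed participants.** With non-informative dropout of 10% vs 40% and no effect, the complete-case ratio was 0.99 to 1.00 and the t test rejected 0.046 of the time. There is no bias in that case, only loss of data. At 15% loss in each arm, 60 × 0.85 = 51 remain. For a true rate ratio of 0.6 (mean 1.0, k = 1.5), power was 35% to 36% for the negative binomial model using everyone, against 30% (t), 25% (Wilcoxon) and 18% (Fisher) in complete cases.

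**4. Overdispersion alone.** With full follow-up, k from 0 to 2 and means of 0.5 and 1.0, the tests rejected 0.045–0.057 (t), 0.047–0.052 (Wilcoxon) and 0.029–0.042 (Fisher) under no effect. None is inflated.

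**5. Is the offset safe?** It assumes a roughly constant rate, yet the Background and Discussion both describe the time just after a fall as high-risk. Suppose cumulative risk grows as the square root of time. A dropout at uniform time then has on average 2/3 of the full count, so expected counts are 1 − d/3. At 10% vs 40% the rates are 0.967/0.95 = 1.018 and 0.867/0.80 = 1.083, a null ratio of 1.06. Simulations with front-loaded risk gave 1.07 to 1.11. The offset then errs in the other direction.

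**6. Enough events for time to first fall?** The expected share with any fall is 1 − (1 + kμ)^(−1/k). For μ = 1, k = 1 it is 0.50, or 60 of 120. For μ = 0.5, k = 2 it is 0.29, or 35 of 120. With complete follow-up, either supports Kaplan-Meier curves and a Cox model with one treatment term.

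**The case against.** The case on the other side is substantial, and parts of it stand.

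- **Overdispersion.** A reader might infer that skewed counts with many zeros invalidate the t, Wilcoxon and Fisher tests. They do not (step 4). A naive Poisson test would fail, but the plan does not use one.
- **Bias in every analysis.** A reader might infer that all the firm analyses are biased whenever dropout differs by arm. Complete-case tests are biased only if dropout is informative (step 3). The article does not say how partial follow-up is handled, and an article may leave that rule to a fuller document. What stands is that neither way of using these tests is satisfactory.
- **Low stakes.** Feasibility is primary and efficacy is secondary and unpowered. With no dropout the power gain is negligible: 0.36 against 0.34 for the t test, at a rate ratio of 0.65 and k = 1. This limits severity. It does not remove the need for a usable estimate, since planning is the declared purpose.
- **Mitigations.** Two-weekly calls, further contact attempts and record review reduce the loss. Record review can recover ED visits, admissions and falls that led to care, at least within the health system. A fall that led to no care would not appear there.
- **Means already give a ratio.** True with complete follow-up. With partial follow-up it is the ratio in step 1.
- **The sample-size condition.** Total N is planned at 120, but support for a model depends on events and achieved recruitment, so caution is reasonable for frailty models. It is not needed for a first-event analysis with one treatment term (step 6).

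**Conclusion.** The point holds in a limited form. The only firm efficacy analyses use no follow-up time and give no rate ratio or dispersion estimate, and ED visits and admissions have no time-based method at all. If partial counts are used as they stand and dropout differs by arm, the null ratio moves to about 0.84 to 0.89 for assumed dropout of 10% versus 30% to 40%. If partly followed participants are dropped instead, the cost is precision, with bias only under informative dropout. Equal dropout does not inflate the tests.

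These sizes rest on assumed event rates, dispersion and dropout, because the article gives none. The bias is smaller than the pilot's own sampling error (step 2). Severity is low to moderate.

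**What to change.** 1. Make the main efficacy estimate for each of the three counts a negative binomial rate ratio with 95% confidence interval, log follow-up time as offset and site as a covariate, and report the dispersion. Define follow-up time separately for each count, since record review may extend beyond the calendars. The simple tests can stay as descriptive support.
2. Run Kaplan-Meier and Cox time to first fall without the sample-size condition. This censors at loss to follow-up and does not need a constant rate. Frailty models can remain optional.
3. For the adjusted analysis, name the covariates in advance from data already collected in both arms, such as prior-fall history and baseline Timed Up and Go, in place of observed baseline differences.

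**Cost.** Analysis work and wording only. Requiring Timed Up and Go before randomisation would be a procedural change and is not proposed. The offset's constant-rate assumption is a real downside, and robust standard errors do not cure it because the problem lies in the estimate. The time-to-first-fall analysis, or splitting follow-up into periods, should serve as the check.

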## Purpose and methods

The GAPcare study aims are to (1) examine the feasibility of the GAPcare intervention by assessing the number of participants who are eligible, recruited, and retained and measure the impact on ED length of stay (LOS); (2) determine if the GAPcare intervention (versus usual care) reduces subsequent falls and ED visits and hospital admissions in the 6-month follow-up; and (3) solicit feedback from participants on the utility and barriers of the GAPcare intervention and collect suggestions for improvement of the intervention. The rationale for completing this pilot trial prior to completing a definitive study powered for efficacy was to assess whether patients, caregivers, and clinicians were open to exploring prevention efforts with our pharmacists and PTs immediately after an injury, whether we could perform the intervention within the time constraints of a typical ED visit, and to obtain initial estimates of efficacy to help us determine the sample size for the subsequent definitive trial.

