### In-ED procedures

After initial evaluation by the ED treatment team, patient participants are asked questions from the baseline questionnaire and their current medications are recorded by the research staff using previously published best practices for medication reconciliation [20]. Intervention patients receive individually tailored pharmacy and PT consultations according to the GAPcare protocol (see Table 1). Intervention participants receive all components of the intervention arm unless they refuse. The research staff delivers the intervention while participants are awaiting results of laboratory testing and imaging (see Fig. 1). Usual care participants receive care as dictated by the ED treatment team alone and a brochure from the Centers for Disease Control and Prevention about home safety. The research staff completes a timed up and go test on all participants regardless of study arm. All participants are provided with a fall calendar that allows them to record any new falls and healthcare visits at the time they occur for the following 6 months. It is at the discretion of the ED treatment team to contact the primary care physician (PCP), consult a case manager, and provide medical equipment (e.g., walkers, canes). Both intervention and usual care participants, their caregivers, and clinicians are asked to complete an end-of-visit survey to record their satisfaction with the care delivery, perceived barriers and facilitators, and suggestions for improvement.

**Table 1 Tab1:** In-ED procedures for intervention patients

Personnel	Description	Administration
Pharmacist assessment and medication-related action plan		
Pharmacist	The pharmacist study protocol consists of the following steps: • Review the research staff obtained medication list [20]. • Perform motivational interviewing with the patient and/or caregiver to identify 1–3 medication recommendations, such as cessation or tapering of medication that increase fall risk. • Communicate the medication-related action plan (MRAP) in writing to the patient and ED treatment team. A facsimile copy of the MRAP is sent to the primary care provider (PCP) at the end of the visit via the newly created EHR structure.	• 20 min • In-person evaluation
Physical therapy assessment and action plan		

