**Fig. 2 Fig2:**
[figure not shown]
Schedule of enrollment, interventions, and assessments. PCP, primary care provider; TUG, Timed Up and Go test; Barthel ADL, Barthel Index for Activities of Daily Living; MRAP, medication-related action plan; SNF, skilled nursing facility

**Table 2 Tab2:** Study instruments and timeline of assessments

Instrument	Description	Administration
Process evaluation		
Screening, eligibility, and retention	• Records how many patients were screened, agreed to participate, were recruited, received intended treatment, and were retained	• Baseline, 180 days
ED component and fidelity	• Records index visit ED LOS, time between consult call and arrival of pharmacist and PT, length of each consult, accuracy and completeness of action plan compared to the protocol	• Baseline
Patient, caregiver, and clinician feedback	• Tracks satisfaction with each component of the evaluation, perceived barriers and facilitators, and collects suggestions for improvement of the intervention	• Baseline
Follow-up component	• Tracks follow-up phone and in-person sessions with the research staff, PT, and any home services. Records uptake of recommendations made on the action plan for intervention participants	• 30, 90, 180 days
Outcome evaluation—feasibility, fidelity, and initial efficacy		
Enrollment questionnaire	• Demographic characteristics (includes marital status, whether the patient lives alone or with others, educational attainment, current employment.) • Prior fall history, comorbidities, ED index visit fall circumstances, and injuries	• Baseline • < 5 min
Six-Item Screener (SIS) [19]	• 6-point questionnaire to measure cognitive impairment for study screening [19], < 4 indicates high risk for cognitive impairment	• Baseline • 2 min
Timed Up and Go (TUG) test [21]	• Timed test of how long it takes the patient to get up from a chair, walk 10 feet, and return to the chair • Validated measure of current function, balance, and fall risk • A TUG > 12 seconds identifies those patients at greater risk for subsequent falls	• Baseline, 180 days • < 5 min
Barthel Index for Activities of Daily Living (ADL) [22]	• Used to assess functional independence [22] • Information can be gained by self-report or caregiver report	• Baseline, 30, 90, 180 days
Tinetti [23]	• Validated measure of gait and balance • Predicts falls	• Baseline • < 5 min
5 Times Sit to Stand [24]	• A measure of functional lower limb muscle strength	• Baseline

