### Data collection

All participants receive an in-ED assessment by the research staff and scheduled follow-ups at 30, 90, and 180 days. Caregiver and clinician interviews occur only during the index ED visit. The information that is collected from participants and the EHR is summarized in Table 2.

We ensure fidelity to the research protocol through several means. First, the study coordinator reviews baseline enrollment data on a weekly basis. Second, the study team reviews on a monthly basis the proportion of subjects who are eligible, approached, consent to participate, and enrolled. Reasons for refusal are tracked to allow the study team to modify how they communicate study details when they approach the participant and for subsequent study planning. The PI holds weekly meetings with the research staff to discuss study progress and address concerns. Finally, the biostatistician performs automated and manual checks in the REDcap data collection program to ensure data quality.

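### Prior fall history is recorded at baseline but named in no efficacy analysis, and the one planned adjustment is tied to baseline differences in physical function: a cheap, low-severity improvement to the recurrent-fall estimates

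*Protocol article*

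**What the plan says.** In the protocol article, Table 2 (Enrollment questionnaire) lists "Prior fall history, comorbidities, ED index visit fall circumstances, and injuries" among the items recorded at baseline. In-ED procedures states that "patient participants are asked questions from the baseline questionnaire" before it turns to what each arm receives, and Data collection adds that "All participants receive an in-ED assessment by the research staff". The history is therefore available in both arms.

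Data analysis, Initial efficacy, sets out the fall comparisons:

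- "We will compare the proportion and median/mean number of recurrent falls, ED visits, and hospital admissions over 6 months" is the stated task, carried out "using Fisher’s exact test (proportions) and Wilcoxon’s and Student’s *t* test (occurrence"). None of these tests uses a covariate.
- If numbers allow, Kaplan-Meier curves, a log-rank test and a Cox model for time to first recurrent fall follow. For the Cox step, "additional analyses will adjust for baseline differences in physical function".
- Frailty models are optional. They would "include random effects that take into account underlying individual predisposition to falling". Prior falls are not named as a covariate there either.

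Purpose and methods gives one reason for the pilot: "to obtain initial estimates of efficacy to help us determine the sample size for the subsequent definitive trial".

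**The concern.** People who have fallen before tend to fall again, and the plan itself acknowledges a personal predisposition to falling. It allows for this only through an unobserved random effect in an optional model, although a measured proxy is already being collected.

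Two features of the stated approach can be improved.

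- **The covariate.** Physical function is named and prior fall history is not.
- **The wording.** Tying adjustment to baseline differences can be read as making it depend on observed imbalance. A covariate is better chosen in advance for its prognostic strength, because it helps even when the arms are balanced. Selection after seeing imbalance makes the adjusted estimate data-driven.

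At stake is the quality of the fall-effect estimate passed to the definitive trial. That trial's planners could also use the strength of the association between prior and later falls, which this plan does not commit to reporting.

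**Working it through.** The article states no precision, power or event count for falls, so there is no figure to reproduce. The inputs taken from it are 120 participants (Sample size), and 1:1 allocation stratified by site only (Recruitment and enrollment). The correlation rho between prior and follow-up falls is not given and is varied as an assumption.

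**1. Room for chance imbalance.** With 60 per arm, the standardized between-arm difference in prior falls has standard error sqrt(2/60) = 0.18. A difference beyond 0.2 SD in either direction corresponds to |z| > 0.2/0.183 = 1.10, which occurs by chance about 27% of the time.

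**2. Mean falls.** Linear adjustment multiplies the variance of the between-arm difference by 1 − rho², so the standard error (SE) by sqrt(1 − rho²). Spending one degree of freedom multiplies the SE by sqrt(118/117) = 1.004. The equivalent unadjusted sample size is 120/(1 − rho²).

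| Assumed rho | Variance factor | SE ratio | SE ratio after 1 df | Equivalent N |
|---|---|---|---|---|
| 0.1 | 0.99 | 0.995 | 0.999 | 121 |
| 0.2 | 0.96 | 0.980 | 0.984 | 125 |
| 0.3 | 0.91 | 0.954 | 0.958 | 132 |
| 0.4 | 0.84 | 0.917 | 0.920 | 143 |
| 0.5 | 0.75 | 0.866 | 0.870 | 160 |

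**3. Check by simulation.** Assumptions: 60 per arm, gamma-Poisson falls, usual-care mean 0.8 falls in 6 months, rate ratio 0.75, frailty variance 1, prior falls entered as log(1 + count), 600 runs per setting. At correlation 0.27 the SD of the estimated mean difference went from 0.210 to 0.202 (ratio 0.962; the formula gives 0.963). At correlation 0.455 it went from 0.195 to 0.181 (ratio 0.928; the formula gives 0.890). The formula is therefore somewhat generous at the upper end.

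**4. Cox model, same simulation, about 49 first falls.**

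- Correlation 0.455: model SE of the log hazard ratio 0.289 unadjusted and 0.292 adjusted. Mean log hazard ratio −0.227 (HR 0.80) unadjusted and −0.263 (HR 0.77) adjusted, against a simulated conditional value of ln 0.75 = −0.288. Rejection rate 0.10 unadjusted and 0.14 adjusted.
- Correlation 0.27: SE 0.289 and 0.291, log hazard ratio −0.209 and −0.219, rejection rate 0.105 in both.

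So the Cox standard error does not fall. The estimate moves away from the null, and power rises modestly only when the correlation is fairly high.

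**5. Cost of three covariates.** With prior falls, one function measure and site entered as one term each, the SE factor if none is prognostic is sqrt(118/115) = 1.013.

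**The case against.** The strongest objection is that this is a condensed article. A fuller covariate list may sit in a full protocol or analysis plan that is not shown, and Initial efficacy does not exclude prior falls. That stands as a limit on the point: it cannot be said that prior falls will go unused. It does not remove the point, because the article does specify an adjustment and its wording, and a better-specified one is available from data already collected.

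A second objection is that physical function is a sensible choice. Table 2 describes Timed Up and Go as a validated marker of fall risk, and In-ED procedures has it done in both arms. Function may carry some of the information in prior falls. The domain is also named in advance, and the reference to differences could mean variation between patients. This is fair: the wording is ambiguous, and it is not shown that covariates would be picked after looking at imbalance.

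Third, the optional frailty model partly addresses predisposition. It does, but a random effect for unmeasured predisposition does not correct a chance imbalance in a measured predictor.

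Three stronger readings are tempting and are not supported:

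- *Every fall estimate is less precise than it could be.* This fails for the Cox model, which is where the adjustment sentence applies. An unadjusted hazard ratio is a marginal quantity and not an error; it is the relevant sizing input if the next trial uses an unadjusted log-rank test.
- *Prior falls are the baseline value of the outcome.* Everyone enters after a fall, and the article gives neither the look-back period nor the scale of the history, so it is a likely predictor and not a like-for-like baseline of the 6-month calendar count.
- *Power gains would be large.* Gains of up to 24 percentage points can be simulated, but only with a rate ratio of 0.5 and predisposition fully shared between the two periods. The documents support neither assumption.

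**Conclusion.** The point holds as a low-severity, low-cost improvement. The fall comparisons are unadjusted, the only named adjustment is for physical function in conditional additional analyses, and a likely predictor collected on all participants is named in no efficacy analysis.

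For mean or rate comparisons, the variance reduction forgone is about 4% at rho 0.2 and 25% at rho 0.5. It is negligible at 0.2 or below and worth having from about 0.4. The size rests wholly on a correlation that the documents do not give. For the Cox model the benefit is a less attenuated, conditional hazard ratio and at most a modest gain in power.

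Feasibility is the primary outcome, and the Discussion says that the trial is not powered for recurrent falls, so no main conclusion is threatened. The point keeps some weight because the efficacy estimates feed the next trial's sample size.

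**What to change.** In Initial efficacy, replace the adjustment sentence with one along these lines: *Between-arm estimates for recurrent falls (difference in mean falls or rate ratio, and hazard ratio if time to first fall is analysed) will also be adjusted for prior fall history as recorded on the enrollment questionnaire, baseline Timed Up and Go, and site. These covariates are fixed in advance and used regardless of observed imbalance. Unadjusted estimates will be shown alongside, and the prior-fall coefficient will be reported.* Timed Up and Go is one suitable named function measure. Site belongs in the model because randomization is stratified by it. The words *differences in* should go.

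The cost is a sentence and a few lines of code, with no new data, patients or staff. Statistically it is a few degrees of freedom, at worst about 1% on the standard error with one term per covariate. Recall error in prior falls reduces the gain; it does not bias the randomized comparison provided it is unrelated to arm, so the history should be taken before allocation is known. The adjusted hazard ratio is conditional rather than marginal and should be labelled as such when it is used for sizing.
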